### Objective and hypothesis

The objective of this trial is to evaluate the feasibility, short-term safety, long-term oncological superiority, and potential benefits of the “no-touch” isolation technique. The hypothesis is that the novel HALS-CME techniques is more consistent with the “no-touch” isolation technique, and is feasible for radical D3 lymphadenectomy, and could offer short-term safety, fast convalescence, and long-term oncological superiority.

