### Secondary outcomes

Secondary endpoints will be measured and recorded prospectively on a case report form (CRF). Intraoperative outcomes include operation time, blood loss, intraoperative complications, and incision length. Pathologic evaluation includes tumor size, grading the plane of surgery (mesocolic plane, intramesocolic plane, muscularis propria plane), length of proximal and distal resection margins, distance between the tumor and the central arterial high tie, distance between the nearest bowel wall and the same high tie, area of mesentery resected, width of the chain of lymph-adipose tissue (the width of the central lymph node region through the high tie), length of the central lymph-adipose chain (the length of the central lymph node region through the high tie), and number of harvested lymph nodes. Postoperative inflammation and immune response (procalcitonin (PCT), C-reactive protein (CRP), interleukin (IL)-6) will be measured at 24 h, 72 h, and 120 h postoperatively. A horizontal visual analogue scale with a 0 to 10 cm scale will be used to measure pain intensity on postoperative days 1, 3, and 5. Postoperative recovery including time to first flatus, liquid diet, and duration of hospital stay will be recorded daily in hospital.

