## Follow-up

The follow-up is consistent with the National Comprehensive Cancer Network (NCCN) guidelines. Within 1 month after surgery, all the consecutive patients in this prospective study will meet the chief surgeon in the outpatient clinic for checking of wounds, recording any complications arising after discharge, and determining the optimal schedule of adjuvant chemotherapy according to the pathohistology. Then 3 months after surgery, and every 3 months for the first 2 years, participants will be followed-up. After 2 years, the surveillance interval will be every 6 months until 3 years or dropout. Data are collected prospectively, including physical examination, blood tests (blood cell count and blood chemistry), tumor markers (carcinoembryonic antigen (CEA), carbohydrate antigen 19-9 (CA 19-9)) every 3 months and CT scans of the chest and abdomen every 6 months. Colonoscopy will be performed 1 year after surgery and will be repeated at 3 years if no lesions are found.

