## Safety and adverse events monitoring

An independent data and safety monitoring board organized by oncologists, gastrointestinal surgeons, and statisticians is responsible for overseeing the progress and safety of the study, including adverse events, morbidity, and drop-outs. All adverse events will be evaluated for severity. Any serious adverse events such as death, disability, and prolonged hospitalization will be recorded on the CRF and reported to the board and the Biological and Medical Ethics Committee of West China Hospital within 24 h. If the number of serious adverse events related to treatment is more than in our own database or as reported by other authors, patient enrollment will be terminated immediately and the Medical Ethics Committee will reassess the safety of the trial. The schedule of study visits and follow-up is shown in Table 1.

**Table 1 Tab1:** Perioperative outcome parameters and schedule of study visits and follow-up

Measures	Preoperative	Intraoperative	Daily in-hospital study visit					Follow-up												
			POD 1	POD 2	POD 3	POD 4	POD 5	M1	M3	M6	M9	M12	M15	M18	M21	M24	M27	M30	M33	M36
Minimally invasive evaluation		X																		
Quality of specimens		X																		
VAS score			X		X		X													
Inflammatory parameters	X		X		X		X													
Short-term recovery			X	X	X	X	X													
Physcial examination	X							X	X	X	X	X	X	X	X	X		X		X
Tumor marker	X							X	X	X	X	X	X	X	X	X		X		X
Abdominal and pelvic CT scan	X									X		X		X		X		X		X
Colonoscopy	X											X				X				X
Adverse event		X	X	X	X	X	X	X	X	X	X	X	X	X	X	X	X	X	X	X

Preoperative study visits will be scheduled within 7 days before surgery

Minimally invasive evaluation includes operation time, blood loss, intraoperative complication, and incision length

Inflammatory parameters including procalcitonin (PCT), C-reactive protein (CRP), and interleukin (IL)-6 will be measured at 24 h, 72 h, and 120 h postoperatively

Short-term recovery including time to first flatus, liquid diet, and duration of hospital stay will be recorded daily in-hospital

Colonoscopy will be performed at 1 year after surgery and will be repeated at 3 years if no lesions are found

Tumor marker includes carcinoembryonic antigen (CEA) and carbohydrate antigen 19-9 (CA 19-9)

*CT* computed tomography, *M* Month, *POD* postoperative day, *VAS* visual analogue scale

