## Sample size and statistical analysis

As the primary aim of the prospective trial is exploratory, no sample size calculation is performed. The statistical tests will be performed in the SPSS software program (version 13.0, SPSS, Chicago, IL, USA). A two-sided *P* value less than 0.05 will be considered statistically significant. Descriptive statistics will be used for baseline demographic and clinical characteristics of participants (i.e., mean and standard deviation for continuous variables, proportions for categorical variables). A χ^2^ test or Fisher’s exact test will be applied for categorical variables. Student’s *t* test or the Mann-Whitney *U* test will be used for continuous variables. Kaplan-Meier curves and log-rank analysis will be used to compare the differences in DFS and OS among the three parallel groups.

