For left-sided colon cancer, exposure and ligation the origin of the inferior mesenteric artery is not difficult, as the TME principles are commonly followed. However, in order to identify the origins of the vessels supplying the right-side colon and perform true D3 lymphadenectomy, the head of the pancreas, the anterior surface of the SMV, and the superior mesenteric artery (SMA) should be fully exposed, which are all technical challenges and more traumatic, leading to longer operation times than the standard operation [21, 22]. The original CME initially described by Hohenberger was performed via a laparotomy. Due to laparoscopic surgery with short- and long-term benefits, there are a series of studies looking at the feasibility of laparoscopic-CME especially for right colon cancer. Finally, although these studies have shown the feasibility and safety of this procedure with acceptable morbidity and oncological outcomes, laparoscopic right hemicolectomy with CME and true center vascular ligation for right colon cancer remains technically challenging especially for obese patients [9, 22, 23].

Since HALS returns the sense of touch to the surgeon, this procedure may represent a valid alternative approach to standard laparoscopy. Furthermore, HALS has been shown to eliminate a substantial part of the technical challenges of standard laparoscopy along with having an acceptable learning curve and reducing operative time, but patient morbidity rates and recovery are comparable with standard laparoscopy [12, 13]. However, this HALS technique allows for hand assistance during laparoscopic surgery and tactile sensation of the lesion, and people argue that this approach is against the “no-touch” isolation technique.

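### Day-5 pain and 120 h markers are scheduled only as in-hospital measurements, so if patients leave before day 5 a test on observed values compares only those who stayed

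*Protocol article*

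**What the plan says.** Five places in the Protocol article bear on this.

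- **Secondary outcomes.** A 0 to 10 cm horizontal visual analogue scale (VAS) "will be used to measure pain intensity on postoperative days 1, 3, and 5". PCT, CRP and IL-6 "will be measured at 24 h, 72 h, and 120 h postoperatively", the last of which falls on day 5. Length of stay is also a secondary outcome: "duration of hospital stay will be recorded daily in hospital".
- **Table 1** (Safety and adverse events monitoring). The columns for days 1 to 5 stand under "Daily in-hospital study visit". After surgery, VAS and the inflammatory parameters are marked on days 1, 3 and 5 and nowhere later. The inflammatory parameters also have a preoperative mark; VAS does not.
- **Follow-up.** The first contact described after discharge is the clinic visit: "Within 1 month after surgery, all the consecutive patients in this prospective study will meet the chief surgeon in the outpatient clinic". Table 1 marks neither VAS nor the inflammatory parameters at month 1.
- **Sample size and statistical analysis.** Continuous variables are compared by Student's t "test or the Mann-Whitney" U test. No longitudinal method is named.
- **Expected recovery.** Objective and hypothesis says the new technique "could offer short-term safety, fast convalescence, and long-term oncological superiority". The Discussion says of hand-assisted surgery in general that "patient morbidity rates and recovery are comparable with standard laparoscopy".

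**The concern.** The only scheduled occasion for a day-5 value is an inpatient visit. A patient who goes home on day 3 or 4 has no scheduled day-5 value, so having one depends on length of stay, which is itself a post-randomisation outcome.

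A two-sample test on whatever day-5 values exist would then no longer compare the randomised groups. It would compare the patients in each arm who were still in hospital. If patients with less pain and less inflammation tend to leave first, the arm that sends more of them home is represented on day 5 by its slower-recovering patients. Its pain and markers would look worse than they are, and a real short-term benefit could be hidden. Day 1 and day 3 are less exposed, because fewer patients can have left by then.

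A later analysis plan cannot recover values that were never collected. It can use the earlier measurements on the same patients, which separate tests at each day do not.

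**Working it through.** The article gives no figure on this point, so there is nothing of its own to reproduce. It states no length of stay, no discharge criteria, no share of patients leaving before day 5, no SD for VAS or markers, and no sample size. The calculation below is an illustration on assumed inputs.

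**Model.** Let R be slowness of recovery, standard normal in every arm, with correlation ρ to the day-5 measurement. The true day-5 means are equal across arms. In each arm the fastest-recovering fraction f leaves before day 5 and has no value. Among those who stay, the mean is shifted upward, in SD units, by

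shift(f) = ρ · φ(z_f) / (1 − f),

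where z_f is the f-quantile of the standard normal and φ its density. The spurious difference between two arms is the difference of their shifts.

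**Assumed inputs.** ρ = 0.3 to 0.5; early-discharge shares of 0%, 5%, 10%, 20% and 30%.

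**The factor multiplying ρ:**

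- f = 0: 0
- f = 5%: 0.1031 / 0.95 = 0.109
- f = 10%: 0.1755 / 0.90 = 0.195
- f = 20%: 0.2800 / 0.80 = 0.350
- f = 30%: 0.3477 / 0.70 = 0.497

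**Spurious difference, arm with more early discharges minus the other:**

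| Shares leaving early | Difference in factor | ρ = 0.3 | ρ = 0.5 |
|---|---|---|---|
| 0% v 0% | 0 | 0 | 0 |
| 10% v 10% | 0 | 0 | 0 |
| 0% v 10% | 0.195 | 0.06 SD | 0.10 SD |
| 5% v 20% | 0.241 | 0.07 SD | 0.12 SD |
| 10% v 30% | 0.302 | 0.09 SD | 0.15 SD |

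A simulation of the same model with 400,000 patients per arm gave the same values.

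**On the VAS scale.** With an assumed SD of 1.0 to 2.0 cm, the last three rows give 0.06 cm (0.195 × 0.3 × 1.0) to 0.30 cm (0.302 × 0.5 × 2.0).

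**Equal shares.** With 10% leaving in each arm, the between-arm difference cancels as long as ρ is the same in both. Each arm's observed day-5 mean is still raised by 0.195 × ρ, or 0.06 to 0.10 SD. That would colour a descriptive plot over days 1, 3 and 5, but the article names no trend test that it would affect.

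**The case against.** The strongest reply is that the bias needs discharges before day 5, and the article reports none. Table 1 schedules inpatient visits through day 5 for everyone, which can be read as an expectation that patients are still in hospital then. This stands. The loss of values is a possibility created by the schedule, and it should not be stated as a fact.

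A reader might also infer that the trial expects earlier discharge after HALS-CME, so that the direction of bias is known. The documents do not support that. The hypothesis speaks of what the technique could offer and mentions neither discharge nor a comparator for recovery, while the Discussion calls recovery after hand-assisted surgery comparable. Nor can it be said that an unblinded team decides discharge. The Discussion says that surgeons, researchers and participants are unblinded, but no section says who decides discharge or on what criteria.

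A third reply is that rules for missing values belong to an analysis plan or full protocol not shown here. That also stands, and their absence is not the point. The point rests on what is printed: a collection schedule tied to inpatient status, and two-sample tests as the only stated method for continuous outcomes.

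Finally, the effect is small. Detecting 0.15 SD with 80% power at two-sided 0.05 needs 2 × (1.96 + 0.84)² / 0.15² ≈ 700 patients per arm, and the outcomes are secondary in a trial that describes its aim as exploratory. This limits the weight of the point. It does not make the observed-value test the better choice, because the alternative uses data already scheduled.

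**Conclusion.** The point holds conditionally. Table 1 ties the day-5 VAS and the 120 h markers to in-hospital visits, no later value is scheduled, and the stated tests make no use of earlier measurements. If patients leave before day 5, a test on observed values compares only those who remain and is biased against any arm with more early discharges, provided faster-recovering patients leave first.

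The illustrative size is 0.06 to 0.15 SD, resting wholly on assumed discharge shares (0% v 10% up to 10% v 30%) and assumed correlations of 0.3 to 0.5. It is zero if nobody leaves early, and zero between arms if equal shares leave with the same correlation.

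The stronger reading, that the day-5 comparison is already selected on recovery and will disfavour HALS-CME, goes beyond the documents. They give neither a length of stay nor a firm expectation that it differs by arm. The matter is minor, affects secondary outcomes only, and leaves the primary endpoints untouched.

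**What to change.** Replace separate tests on observed values with one repeated-measures mixed model per outcome over days 1, 3 and 5, with arm, day and their interaction. Log-transform PCT, CRP and IL-6 and adjust each for its preoperative value, which Table 1 already schedules. VAS has no preoperative measurement, so its model uses the three postoperative days alone. The day-5 contrast is then read from the model. Report by arm the number of patients with a day-5 value and the number still in hospital on day 5, so that a reader can see whether selection is an issue at all.

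This needs no new visits or samples. The model uses days 1 and 3 when day 5 is missing, and the baseline adjustment gains precision for the markers even when nothing is missing. The price is an assumption that missing day-5 values are predictable from the earlier ones; to the extent that discharge depends on something those values do not capture, some bias remains.

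A telephone pain score and a switch to 72 h as the main marker comparison are not required. A horizontal 10 cm scale cannot be marked over the telephone, a call does nothing for blood markers, and the choice of main time point is for the sponsor.

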## Follow-up

The follow-up is consistent with the National Comprehensive Cancer Network (NCCN) guidelines. Within 1 month after surgery, all the consecutive patients in this prospective study will meet the chief surgeon in the outpatient clinic for checking of wounds, recording any complications arising after discharge, and determining the optimal schedule of adjuvant chemotherapy according to the pathohistology. Then 3 months after surgery, and every 3 months for the first 2 years, participants will be followed-up. After 2 years, the surveillance interval will be every 6 months until 3 years or dropout. Data are collected prospectively, including physical examination, blood tests (blood cell count and blood chemistry), tumor markers (carcinoembryonic antigen (CEA), carbohydrate antigen 19-9 (CA 19-9)) every 3 months and CT scans of the chest and abdomen every 6 months. Colonoscopy will be performed 1 year after surgery and will be repeated at 3 years if no lesions are found.

## Safety and adverse events monitoring

An independent data and safety monitoring board organized by oncologists, gastrointestinal surgeons, and statisticians is responsible for overseeing the progress and safety of the study, including adverse events, morbidity, and drop-outs. All adverse events will be evaluated for severity. Any serious adverse events such as death, disability, and prolonged hospitalization will be recorded on the CRF and reported to the board and the Biological and Medical Ethics Committee of West China Hospital within 24 h. If the number of serious adverse events related to treatment is more than in our own database or as reported by other authors, patient enrollment will be terminated immediately and the Medical Ethics Committee will reassess the safety of the trial. The schedule of study visits and follow-up is shown in Table 1.

**Table 1 Tab1:** Perioperative outcome parameters and schedule of study visits and follow-up

Measures	Preoperative	Intraoperative	Daily in-hospital study visit					Follow-up												
			POD 1	POD 2	POD 3	POD 4	POD 5	M1	M3	M6	M9	M12	M15	M18	M21	M24	M27	M30	M33	M36
Minimally invasive evaluation		X																		
Quality of specimens		X																		
VAS score			X		X		X													
Inflammatory parameters	X		X		X		X													
Short-term recovery			X	X	X	X	X													
Physcial examination	X							X	X	X	X	X	X	X	X	X		X		X
Tumor marker	X							X	X	X	X	X	X	X	X	X		X		X
Abdominal and pelvic CT scan	X									X		X		X		X		X		X
Colonoscopy	X											X				X				X
Adverse event		X	X	X	X	X	X	X	X	X	X	X	X	X	X	X	X	X	X	X

Preoperative study visits will be scheduled within 7 days before surgery

Minimally invasive evaluation includes operation time, blood loss, intraoperative complication, and incision length

Inflammatory parameters including procalcitonin (PCT), C-reactive protein (CRP), and interleukin (IL)-6 will be measured at 24 h, 72 h, and 120 h postoperatively

Short-term recovery including time to first flatus, liquid diet, and duration of hospital stay will be recorded daily in-hospital

Colonoscopy will be performed at 1 year after surgery and will be repeated at 3 years if no lesions are found

Tumor marker includes carcinoembryonic antigen (CEA) and carbohydrate antigen 19-9 (CA 19-9)

*CT* computed tomography, *M* Month, *POD* postoperative day, *VAS* visual analogue scale

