## Methods and design

### Study design and setting

This is a single-center, open-label, noninferiority, randomized controlled trial undertaken at West China Hospital of Sichuan University (Chengdu, Sichuan, China), which performs 2000 colorectal cancer resections per year. The chief surgeon performs more than 400 laparoscopic-colorectal cancer resections per year. Participants will be randomly assigned to three parallel groups at a 1:1:1 ratio using a centralized randomization list. Patients assigned to the HALS-CME group will receive the hand-assisted laparoscopic surgery with CME, D3 lymphadenectomy, and total “no-touch” isolation technique (HALS-CME). Patients in the LAP-CME group will receive laparoscopic surgery with CME, D3 lymphadenectomy, and total “no-touch” isolation technique. Meanwhile, patients in cLAP group will receive conventional laparoscopic surgery with CME and D3 lymphadenectomy (Fig. 1). Blood samples and peritoneal washes will be collected from each participant during the operative procedure. Recruitment began on December 2015, and the trial is expected to proceed for 3 years.

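### The safety halt compares a number of serious events with an unnamed reference, without a denominator or any allowance for chance, so its behaviour depends on which reference is picked

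*Protocol article*

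**What the plan says.** All of the following is in the protocol article.

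- **Trigger** (Safety and adverse events monitoring): "If the number of serious adverse events related to treatment is more than in our own database or as reported by other authors".
- **Consequence** (same section): "patient enrollment will be terminated immediately and the Medical Ethics Committee will reassess the safety of the trial". Enrolment ends first and the reassessment follows.
- **Oversight** (same section): an independent board that includes statisticians "is responsible for overseeing the progress and safety of the study, including adverse events, morbidity, and drop-outs". Serious events are to be "reported to the board and the Biological and Medical Ethics Committee of West China Hospital within 24 h". The halting sentence does not say who applies the trigger, or when.
- **Trial size** (Sample size and statistical analysis): "As the primary aim of the prospective trial is exploratory, no sample size calculation is performed". No monitoring method is given there.
- **Arms** (Study design and setting): "Participants will be randomly assigned to three parallel groups at a 1:1:1 ratio using a centralized randomization list". The halting sentence mentions no arm.
- **Possible guides to the size of the centre's database** (Study design and setting): the hospital is one "which performs 2000 colorectal cancer resections per year", and "The chief surgeon performs more than 400 laparoscopic-colorectal cancer resections per year". The article does not say which operations or years the database covers.

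**The concern.** The sentence fixes the statistic (a number), the comparator (either of two sources, neither identified), the threshold (anything above) and the consequence (an automatic halt). It is therefore a stated rule that can be examined as it stands. It is not a detail left for a charter or a fuller protocol.

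Three things are wrong with it.

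1. A number of events means little without the number of patients behind it, and the trial and its references will differ in size.
2. The two comparators are joined by *or*, with nothing to settle the case where they disagree.
3. Even if number is read as rate, any excess over the benchmark is enough, however small and however often it is checked.

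At stake is the only halting rule in the article. Depending on the reading, it could stop recruitment for noise or stay silent through a real excess. Two careful people applying it to the same data could reach opposite answers.

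**Working it through.** The article gives no reference rate, threshold or error rate for the halt, so there is no stated figure to reproduce. I computed how the rule behaves under assumed inputs, treating each patient as having or not having a treatment-related serious event.

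**Inputs.** From the article: three arms at 1:1:1; more than 400 and 2000 resections a year as rough guides to database size. Assumed: reference rate p0, trial size N, reference size M and look schedule.

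**1. Count reading.** The reference series holds c = M × p0 events. With X ~ Binomial(N, m × p0), where m is the true rate as a multiple of the reference, the rule fires with probability P(X ≥ c + 1).

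| M | p0 | c | N | m = 1 | m = 2 | m = 3 |
|---|---|---|---|---|---|---|
| 2000 | 5% | 100 | 90 to 300 | 0.00 | 0.00 | 0.00 |
| 2000 | 10% | 200 | 90 to 300 | 0.00 | 0.00 | 0.00 |
| 400 | 5% | 20 | 150 | 0.00 | 0.07 | 0.67 |
| 400 | 5% | 20 | 300 | 0.08 | 0.97 | 1.00 |
| 100 | 5% | 5 | 90 | 0.29 | 0.90 | 1.00 |
| 100 | 5% | 5 | 150 | 0.77 | 1.00 | 1.00 |
| 100 | 10% | 10 | 90 | 0.29 | 0.98 | 1.00 |
| 100 | 10% | 10 | 150 | 0.89 | 1.00 | 1.00 |

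With M = 100 and N = 300, the m = 1 figure is above 0.99 at both rates. The size of the reference, which the article leaves open, decides the answer. The row with M = 400 and N = 300 behaves tolerably, but nothing in the article secures those sizes.

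**2. Rate reading, no true excess.** The rule fires when X/n > p0 while the true rate equals p0. For one look at the end, the smallest firing count is r = floor(N × p0) + 1 and the probability is P(X ≥ r). For repeated checking I simulated 40,000 binomial paths and counted those above p0 at any check from patient 20 onward.

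| p0 | N | r | One look | Every patient from the 20th |
|---|---|---|---|---|
| 5% | 50 | 3 | 0.46 | 0.62 |
| 10% | 50 | 6 | 0.38 | 0.68 |
| 15% | 50 | 8 | 0.48 | 0.70 |
| 5% | 100 | 6 | 0.38 | 0.75 |
| 10% | 100 | 11 | 0.42 | 0.78 |
| 15% | 100 | 16 | 0.43 | 0.80 |

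So the false-halt probability is 38% to 48% at one look and 62% to 80% with continual checking. As an intermediate case, four equally spaced looks give 0.61 to 0.74 (p0 from 2% to 15%, N from 60 to 300).

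**3. By arm or pooled.** Suppose the benchmark and both control arms are at 10% and HALS-CME is at 20%. The pooled rate is (10 + 10 + 20)/3 = 13.3%, so an excess of 10 points shrinks to 3.3. For the no-margin rule at one final look, the pooled probability is P(X1 + X2 > 0.10 × N), with X1 ~ Binomial(N/3, 0.20) and X2 ~ Binomial(2N/3, 0.10). The by-arm probability is P(X1 > 0.10 × N/3).

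| N | Pooled | HALS-CME alone |
|---|---|---|
| 60 | 0.71 | 0.79 |
| 99 | 0.87 | 0.92 |
| 150 | 0.86 | 0.95 |
| 300 | 0.95 | 0.99 |

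With no margin, pooling costs little detection. The cost grows once chance is allowed for. As an illustration only, take the smallest count t with P(X ≥ t) ≤ 0.05 at a 10% rate:

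- N = 60: t is 11 pooled and 5 of 20 in the arm; detection is 0.17 against 0.37.
- N = 300: t is 40 pooled and 16 of 100 in the arm; detection is 0.53 against 0.87.

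**The case against.** The best defence has four parts.

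- **The article is a condensed text.** Look schedules, bounds and by-arm tables usually sit in a board charter, which is not shown, and an independent board with statisticians receives every serious event. This stands for the schedule and the tables, and I do not count their absence as a fault. It does not rescue the sentence. A charter that added a denominator, a margin or a board review before the halt would contradict what is printed.
- **A false trigger leads to human review by the ethics committee.** It biases no estimate and decides no endpoint. That is right, and it limits the severity.
- **The magnitudes rest on assumptions.** The benchmark, trial size and look schedule are all mine, and the 24-hour duty concerns reporting events, not testing after each patient. That also stands. The conclusion does not need continual checking, since one look already gives 38% to 48%.
- **Stronger readings go too far.** A reader might infer that the rule can never fire and so protects nobody, because the trial cannot match the event count of a 2000-resection centre. The article does not support this: published reports are an alternative comparator and may be small, and the annual volume of all colorectal cancer resections is not the stated size of the database. A reader might also infer that the rule pools the arms and would hide harm from HALS-CME. The text is silent on arm, it does not prescribe pooling, and with no margin a pooled check would still fire with probability 0.71 to 0.95 in the doubling scenario.

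**Conclusion.** The point holds as a badly specified rule that should be fixed. As a count, the rule ranges from practically never firing (2000-patient reference, up to triple the rate) to firing with probability 0.29 to above 0.99 with no excess (100-patient reference), at assumed rates of 5% and 10% and 90 to 300 trial patients. Between these it works tolerably only by accident of size. As a rate with no excess, it halts enrolment with probability 38% to 48% at one look and 62% to 80% with a check after every patient from the 20th, at assumed benchmarks of 5% to 15% and 50 to 100 patients. Silence on arm is a secondary weakness, modest under the present wording and larger once a margin is added. Confidence is high on the wording. The probabilities are conditional on the assumed ranges.

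**What to change.** Rewrite the halting sentence so that it:

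- compares the proportion of patients with a treatment-related serious event, by arm;
- uses one reference, named in advance with its patient population and denominator;
- applies at scheduled looks;
- uses a prespecified bound that allows for chance, such as an exact binomial or Bayesian bound;
- triggers review by the existing board when the bound is crossed.

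The board should set the reference, looks and bound, and tabulate the false-trigger and detection probabilities for the planned arm sizes. This review proposes no threshold.

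The cost is one paragraph in the protocol and one table in the board's charter. The small downside is that the bound has to be agreed in advance.
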